#### Other Outcomes

Other outcomes include: anxiety (using the Generalised Anxiety Disorder Scale; GAD-7) [37], sleep quality (using the Pittsburgh Sleep Quality Index; PSQI) [38], disability (using the World Health Organisation Disability Assessment Scale; WHODAS) [39], illness perception (using the Brief Illness Perception Questionnaire; BIPQ) [40], participation in physical activity (using the Active Australia Baseline Survey; AABS) [41] and alcohol use (using the Alcohol Use Disorders Identification Test - Consumption; AUDIT-C) [42]. Medication use for CVD and depression will also be determined, in addition to workforce and social participation. Satisfaction with treatment and reasons for drop-out will also be measured. Help-seeking using scales measuring actions to overcome depression, preferences for treatment type and expectations of the trial will be measured using previously developed formats [29,43]. User behaviour (e.g. time on site, number of modules completed, length of individual module use and frequency of access) will be tracked for both the *e-couch *and *HealthWatch *programs. In addition, demographic and past medical history data derived from the *45 and Up Study *baseline dataset will be available for analysis.

Refer to Table 2 for a list of all outcomes to be assessed.

### Blinding and allocation concealment

The investigators, analysts, trial manager and all participants will be blinded to treatment allocation for the duration of the trial. Only the internet program system administrator will have access to un-blinded data at the individual level however they will not have any contact with trial participants.

Treatment allocation will be preserved by virtue of the intervention delivery method being web-based, in addition to all of the follow-up assessments. Where participants are unable to complete follow-up assessments online, they will be conducted over the telephone by a Research Assistant who will be blinded to allocation. In the event that treatment allocation is revealed to the Research Assistant during the six-month follow-up assessment, the subsequent 12-month follow-up assessment will be conducted by a secondary Research Assistant, who will also be blinded to allocation.

### Statistical Methods

#### Sample Size

We will randomly select 8,000 of those meeting trial eligibility criteria from the *45 and Up Study *to participate. A conservative return rate of 20% is expected from this invitation on the basis of results of previous population-based internet trials [44]. Further assuming that only 40% of those agreeing to potentially participate actually consent after having responded or become un-contactable over a one-month period or currently do not demonstrate depressive symptoms or have access to counselling, this leaves a potential sample of about 640. Taking into account a 20% attrition rate post-randomisation, this will provide a final sample of approximately 510.

#### Power Calculation

To detect an effect size of 0.3 standard deviations as the difference between randomised groups in mean change in depressive symptom scores at three-months, with α = 0.05 and β = 0.90, the required sample size for the trial is 470.

#### Statistical Analyses

The primary a priori outcome is change in depressive symptoms between baseline and three-months as measured by the PHQ-9 score. However, internet trials often have missing data. Analyses of the change in this continuous measure will be undertaken on an intention-to-treat basis, including all participants randomised regardless of treatment actually received or withdrawal from the study. Mixed-model repeated measures (MMRM) analyses will be used since this approach can include participants with missing data and incorporate data from intermediate measurement time points of four and eight weeks. Mixed-models yield unbiased and efficient estimates under MCAR (missing completely at random) and MAR (missing at random) assumptions, which are often reasonable in clinical trials. Additional analyses will explore participant characteristics which moderate outcome and, if appropriate, levels of presenting severity associated with significant improvement. The latter analyses will use a Johnson-Neyman approach [45].

A completers analysis on all participants completing at least 75% of the internet modules and all measures will be undertaken as a secondary analysis. Sensitivity analyses based on multiple imputation and on assuming all drop outs are non-responders (worst case scenario) will be undertaken.

The secondary outcomes of change in the continuous measures of cognitive function and self-reported adherence will be analysed in the same way.

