#### Randomisation

Randomisation will be undertaken using a customised and fully automated randomisation facility built into the trial website. Participants will be randomised to receive either the intervention program (*e-couch*) or the active control program (*HealthWatch*). Randomisation will be stratified by depressive symptom severity using specified block sizes of eight. Symptom severity will be determined using PHQ-9 scores, where scores ranging from 8 to 14 are classified as moderate depressive symptoms, and scores ranging from 15 to 27 are classified as major depressive symptoms. The computerised procedure allows for full replication.

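### The sensitivity analysis labelled worst case, with all drop-outs in both arms as non-responders, is not the worst case for the treatment difference and can favour e-couch

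*Protocol article*

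**What the plan says.** In the Protocol article, Statistical Analyses, the endpoint is continuous: "The primary a priori outcome is change in depressive symptoms between baseline and three-months as measured by the PHQ-9 score". The section then remarks: "However, internet trials often have missing data". It chooses an intention-to-treat mixed model for repeated measures (MMRM) that also uses the week 4 and week 8 measurements, and justifies it under data missing completely at random or MAR.

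The sensitivity analyses are fixed in one sentence: "Sensitivity analyses based on multiple imputation and on assuming all drop outs are non-responders (worst case scenario) will be undertaken". The article states neither an imputation model nor the PHQ-9 change that a non-responder receives. Listed apart from these, as a secondary analysis, is the following: "A completers analysis on all participants completing at least 75% of the internet modules and all measures will be undertaken". Cognition and adherence are to be handled in the same manner as PHQ-9.

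The Sample Size section gives attrition for the whole trial only: "Taking into account a 20% attrition rate post-randomisation, this will provide a final sample of approximately 510". It is not split by arm.

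**The concern.** The primary result rests on MAR. The named analyses should therefore show how far the estimate moves if drop-outs did worse than MAR predicts, above all in the e-couch arm.

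Multiple imputation done in the standard way makes the same assumption as the MMRM, so agreement between the two says little about departures from it. That leaves the non-responder rule. Because it is applied to both arms, it penalises HealthWatch drop-outs as well as e-couch drop-outs. Participants enter with PHQ-9 of 8 or more, so some improvement in both arms is plausible. If HealthWatch then loses more people, the rule removes more improvement from the control arm and pushes the difference towards e-couch. A reader who sees a positive result survive a worst case would take more reassurance than the analysis can give.

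**Working it through.** **Inputs from the Protocol article**
- Target difference 0.3 SD at three months; "with α = 0.05 and β = 0.90, the required sample size for the trial is 470" (Power Calculation).
- About 640 randomised and 20% attrition overall (Sample Size).
- Two arms, blocks of eight (Randomisation). The ratio is not stated, so I assume 1:1, or 320 per arm.

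**The plan's own figures.** Reading the 0.90 as power, two-sided: 2 × (1.960 + 1.282)² / 0.3² = 233.5, so 234 per arm and 468 in total. The t-test version gives 235 per arm, 470 in total. Recruitment: 8,000 × 0.20 × 0.40 = 640, and × 0.80 = 512. These reproduce and are not in question.

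**Assumptions.** Improvement is positive, in SD units of the change score. A non-responder has zero change. HealthWatch improves by m, and e-couch by m plus the true effect. Drop-out is dE (e-couch) and dC (HealthWatch). The article gives neither m nor drop-out by arm.

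**1. No true effect.** Estimate = (1 − dE)m − (1 − dC)m = m(dC − dE).
- m = 1, dE = 0.15, dC = 0.25: bias = 1 × 0.10 = 0.10 SD towards e-couch.
- Variance per arm after fill-in at m = 1 is 1 − d², that is 0.9775 and 0.9375. SE = √[(0.9775 + 0.9375)/320] = 0.0774, and 0.10/0.0774 = 1.29. The chance of exceeding 1.96 is about 25%; simulation of 4,000 trials gave 26.0%.
- m = 0.5, same drop-out: bias 0.05 SD; 10.2% in simulation.
- Equal drop-out: about 2.5%, which is nominal.
- Reversed (25% e-couch, 15% HealthWatch): bias −0.10 SD; e-couch significant in about 0.1%.

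**2. True effect 0.3 SD.** Estimate = (1 − dE)(m + 0.3) − (1 − dC)m = 0.3 + m(dC − dE) − 0.3dE. It exceeds 0.3 only if dC/dE > 1 + 0.3/m.

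| m | dE / dC | dC/dE | Threshold | Estimate (SD) |
|---|---|---|---|---|
| 0.5 | 20% / 20% | 1.00 | 1.60 | 0.24 |
| 0.5 | 16% / 24% | 1.50 | 1.60 | 0.292 |
| 0.5 | 15% / 25% | 1.67 | 1.60 | 0.305 |
| 0.5 | 10% / 30% | 3.00 | 1.60 | 0.37 |
| 0.5 | 30% / 10% | 0.33 | 1.60 | 0.11 |
| 1.0 | 18% / 22% | 1.22 | 1.30 | 0.286 |

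**3. Is it the worst case?**
- Continuous, m = 0.5, 20% drop-out per arm: zero change in both arms gives 0.24. Zero change for e-couch drop-outs only, with HealthWatch drop-outs improving like those observed, gives 0.80 × 0.80 − 0.50 = 0.14, already less favourable.
- Binary reading, assumed response 50% v 36% and 20% missing per arm: non-response in both arms gives 0.8 × 50 − 0.8 × 36 = +11.2 points. The extreme (e-couch drop-outs fail, HealthWatch drop-outs respond) gives 40 − (28.8 + 20) = −8.8 points.

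The label fails on either reading.

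**4. What a graded analysis would show.** Take an observed effect of 0.30 SD and 320 per arm, with e-couch drop-outs worse than MAR predicts by δ. Estimate = 0.30 − dE × δ.
- 20% missing per arm: SE = √(1/256 + 1/256) = 0.0884. Significance is lost at δ = (0.30 − 1.96 × 0.0884)/0.20 ≈ 0.63 SD; the effect reaches zero at 0.30/0.20 = 1.5 SD.
- 30% e-couch, 20% HealthWatch: SE = 0.0915. The corresponding values are about 0.40 SD and 1.0 SD.
- Imputing e-couch drop-outs at the HealthWatch mean gives 0.30(1 − dE), or 0.24 at 20%, whatever m and dC are.

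Neither of these analyses can raise the estimate above the observed 0.30.

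**5. Completers (minor).** With no true effect, assumed completion of 45% e-couch v 65% HealthWatch and correlation 0.3 between completing and outcome, the bias is 0.3 × [φ(c)/p at 0.45 − φ(c)/p at 0.65] = 0.3 × (0.880 − 0.570) = 0.093 SD. Here p is the completion proportion, c its normal cut-point and φ the normal density. The direction depends on which arm completes less.

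**The case against.** Several stronger readings are tempting, and the documents do not support them.

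- **The plan cannot test MAR, or has no check outside it.** No analysis can test MAR from the observed data. The non-responder rule is itself a departure from MAR. It is a single fixed scenario, but it exists.
- **The rule is conservative only if e-couch loses more people.** Not so. With a true 0.3 SD effect it stays below 0.3 at equal drop-out (0.24), and still does so with moderately higher HealthWatch drop-out.
- **About a quarter of such trials would wrongly declare e-couch superior.** The MMRM is primary. When the scenario was re-simulated with random drop-out, a complete-case comparison standing in for the MAR analysis favoured e-couch in only 2.7%. The 26% describes a misleading supporting analysis, not the trial's error rate.
- **Filling in a constant understates variance.** At equal drop-out the error rate stays about 2.5%, so no consequence is shown.
- **Multiple imputation merely repeats the MMRM.** That is the usual default, not stated text. Imputation could draw on module use, anxiety or medical history, all listed under Other Outcomes, and so condition on more than the MMRM does.
- **The completers analysis is offered as a missing-data check.** The article calls it secondary and lists it separately.
- **The protocol expects substantial missing data.** It says such data are common in internet trials and plans for 20% attrition.

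It is also fair to say that the non-responder value and the imputation model may be set in a statistical analysis plan that is not shown, so their absence alone is not a fault. What stands is the label: the article states that a rule applied to all drop-outs is the worst case, and for a between-arm difference it is not.

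**Conclusion.** The point holds in limited form. The only named departure from MAR is mislabelled, and with zero change as the fill-in its direction depends on which arm loses more people. The 0.10 SD figure and the 26% rest on assumed drop-out of 15% v 25%, 1 SD improvement in both arms, zero change for drop-outs and 1:1 allocation. At 0.5 SD improvement they fall to 0.05 SD and 10%, and with reversed drop-out the rule works against e-couch. That the label is wrong depends on none of these figures.

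The primary MMRM and the sample size of 470 are unaffected. What needs repair is the claim of robustness: no named analysis varies the departure from MAR over a range, although with 20% missing per arm a departure of about 0.63 SD among e-couch drop-outs would be enough to remove significance from an observed 0.30 SD.

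**What to change.** 1. Remove the worst-case label and replace the non-responder rule with delta-adjusted multiple imputation of three-month PHQ-9. Worsen imputed values for e-couch drop-outs in steps until significance is lost, and report that tipping point.
2. Add one reference-based run that imputes e-couch drop-outs from HealthWatch.
3. As a minor change, keep people with a valid PHQ-9 in the completers analysis of PHQ-9 even if another measure, such as a cognitive test, is missing. Describe that analysis as a non-randomised, descriptive comparison.

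A complier-average estimate is optional and not a clear improvement. It requires that people below 75% of modules gain nothing. With 12 modules, someone who finishes eight (67%) falls below the threshold yet has received most of the program. At an assumed 45% completion, 0.30 SD becomes 0.30/0.45 = 0.67 SD, which is inflated if partial users benefit.

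The cost is some extra analysis of data already collected. The robustness statement may also turn out less favourable.

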### Ethical Considerations

The trial will be undertaken in compliance with the World Medical Association Declaration of Helsinki (revised version of Seoul, 2008), international standards of Good Clinical Practice (GCP) and the applicable regulatory requirements in Australia. The design and implementation of the trial has been approved by The University of Sydney Human Research Ethics Committee (Reference Number: 06-2009/11800).

The trial is bound by Commonwealth and State privacy legislation and guidelines within Australia, including the Health Records and Information Privacy Act 2002. All research data collected including survey responses, cognitive testing results and website activity data will be identified by the Trial ID numbers only. All files linking participant names and contact information to Trial ID numbers will be stored separately from raw research data. All research data collected will be stored on a secure server at the Brain & Mind Research Institute, The University of Sydney. The server will be password protected and access permitted by authorised research staff only.

A suicide/self-harm risk protocol is in place, which includes a list of emergency sources of help. If participants wish to seek treatment elsewhere, they will be advised to speak to their regular general practitioner or will be provided with information to locate an appropriate general practitioner in their local area. A referral list of appropriate health professionals and services is in place.

## Discussion

This trial will bring together a multidisciplinary perspective from psychiatry, cardiology, psychology, neuropsychology and neurology to study links between depression, CVD and cognitive function using a novel intervention. The trial will be one the first of its kind to evaluate the efficacy of a web-based intervention for depression in people aged 45 years and over with significant depressive symptoms who are also being treated for cardiovascular risk factors. In particular, this trial will target people across the range of CVD, especially those in early stage and those hard to access through usual clinical channels.

The intervention itself (*e-couch*) is evidence-based and can be rolled out in a high fidelity manner on a large scale at low cost. It has the capacity to attract those who don't usually seek health care services and to be delivered in areas with limited access, such as rural and remote regions. Further, this will be the first study to evaluate the effect of treating depression on early cognitive impairment, using a novel internet based assessment. The trial will also assess the effect of intervening on people's mood upon adherence to treatment and lifestyle factors important in secondary cardiovascular disease prevention. It will enable exploration of mechanisms by which these may occur in future studies.

The study addresses an Australian national health priority (ageing well, ageing productively). With health reforms placing preventative services at the centre of health efforts, such a scalable intervention may, if efficacious, have an important role in the amelioration of the burgeoning impact of dementia.

## Abbreviations

AABS: Active Australia Baseline Survey; AUDIT-C: Alcohol Use Disorders Identification Test; BIPQ: Brief Illness Perception Questionnaire; CBT: Cognitive Behavioural Therapy; CREDO: Cardiovascular Risk E-couch Depression Outcome; CVD: Cardiovascular Disease; ECG: Electrocardiogram; GAD-7: Generalised Anxiety Disorder Scale; GCP: Good Clinical Practice; IPT: Interpersonal Psychotherapy; K-10: Kessler Psychological Distress Scale; MAR: Missing At Random; MCAR: Missing Completely At Random; MMRM: Mixed-Model Repeated Measures; MOS: The Medical Outcomes Study Measures of Patient Adherence; OECD: Organisation for Economic Co-operation and Development; PHQ-9: Patient Health Questionnaire; PSQI: Pittsburgh Sleep Quality Index; RCT: Randomised Controlled Trial; WHODAS: World Health Organisation Disability Assessment Scale.
